***Healthcare utilisation***
Maternal blood or urine testing at the laboratory prior to birth admission
Foetal cardiotocography
Foetal ultrasound
Number of outpatient visits - General practitioner - Antenatal clinic visit - Obstetric medicine clinic visits
Number of medical, day, or maternity assessment unit visits
Acute care area for urgent/emergent visit other than in labour - Emergency department - Birthing unit presentations
Number of antenatal admission days prior to birth
***Feasibility and acceptability***
Compliance with remote monitoring *(interventional arm only)*
Compliance with face to face consultations
Number of phone calls from the investigator *(interventional arm only)*
Recruitment rate
Persistence with remote monitoring
***Quality of life and patient satisfaction***
EuroQol 5D survey
State Trait Anxiety Inventory questionnaire
Edinburgh Postnatal Depression Score questionnaire
Investigator-designed remote monitoring feasibility surveys (*interventional arm only*)
Qualitative interview with participants and clinicians *(interventional arm only)*

The satisfaction and quality of life of every participant will be surveyed with the EuroQol-5D-3L [41], State Trait Anxiety Inventory [42] and Edinburgh Postnatal Depression Score questionnaires [43]. Surveys will be sent by email at study baseline, at 28 weeks’ gestation and 6 weeks after delivery. Additionally, participants in the interventional arm will complete investigator-designed surveys to assess the technological feasibility of remote monitoring.

Qualitative interviews will be undertaken after the endpoint of the study using a mixed-methods approach, focusing on the experiences of clinicians and midwives involved in the study, as well as a group of consented participants from the interventional arm. Interviews will be conducted either in person or through virtual video conference, by an investigator not previously known to the participants during their pregnancy. All audio from the interviews will be recorded to allow for transcription, and numbers of participant to be determined by assessment of data saturation.

Australia has a universal healthcare system and as such Medicare is a national system that funds and also collects accurate data regarding episodes of health care delivery in the community including investigations, admissions, primary health review and medication prescription. Therefore, utilisation of healthcare resources will be assessed through collection of data from the Medicare Benefits Schedule (MBS) and Pharmaceutical Benefits Schedule (PBS). The cost-effectiveness of remote blood pressure monitoring will be assessed from the perspective of both patients and the healthcare system based on this data.

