## Abstract

**Background:**

Pregnant women at high risk for developing a hypertensive disorder of pregnancy require frequent antenatal assessments, especially of their blood pressure. This expends significant resources for both the patient and healthcare system. An alternative to in-clinic assessments is a remote blood pressure monitoring strategy, in which patients self-record their blood pressure at home using a validated blood pressure machine. This has the potential to be cost-effective, increase patient satisfaction, and reduce outpatient visits, and has had widespread uptake recently given the increased need for remote care during the ongoing COVID-19 pandemic. However robust evidence supporting this approach over a traditional face-to-face approach is lacking, and the impact on maternal and foetal outcomes has not yet been reported. Thus, there is an urgent need to assess the efficacy of remote monitoring in pregnant women at high risk of developing a hypertensive disorder of pregnancy.

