**Methods:**

The REMOTE CONTROL trial is a pragmatic, unblinded, randomised controlled trial, which aims to compare remote blood pressure monitoring in high-risk pregnant women with conventional face-to-face clinic monitoring, in a 1:1 allocation ratio. The study will recruit patients across 3 metropolitan Australian teaching hospitals and will evaluate the safety, cost-effectiveness, impact on healthcare utilisation and end-user satisfaction of remote blood pressure monitoring.

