## Methods

In the “REMOTE blood pressure monitoring in high-risk pregnant women — a randomised controlled trial” (REMOTE CONTROL trial), a pragmatic non-inferiority unblinded multicentre randomised controlled trial, we aim to determine whether remote BP monitoring in pregnant women at high risk for developing a HDP is as safe as conventional clinic BP monitoring. We will evaluate foetal outcomes as the primary outcome, in addition to maternal outcomes, patient satisfaction and the cost-effectiveness of this strategy. This study protocol follows the SPIRIT reporting guidelines [37].

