### Outcome measures

The primary outcome is perinatal mortality and morbidity, represented by a composite adverse foetal outcome. The composite adverse foetal outcome is defined as: perinatal loss (miscarriage, pregnancy termination, stillbirth or neonatal death), high-level neonatal care (admission to neonatal intensive care unit or special care nursery for > 48 h) or small-for-gestational age (birthweight below the 10th centile). All components of the composite outcome will be assessed separately individually as secondary outcomes. Other secondary outcomes will consist of maternal outcomes, feasibility and patient satisfaction, quality of life, healthcare utilisation and cost-effectiveness (Table 3).

**Table 3 Tab3:** Secondary outcomes

*General*
Rate of composite maternal complications (adapted from the International Collaboration to Harmonise Outcomes for Pre-eclampsia [40]: - Maternal mortality - Eclampsia - Stroke -Cortical blindness - Retinal detachment - Pulmonary oedema - Acute kidney injury - Liver capsule haematoma or rupture - Placental abruption - Postpartum haemorrhage - Raised liver enzymes - Haemolysis - Low platelets - Admission to the intensive care unit - Intubation/mechanical ventilation
Gestational age at delivery
Birthweight
APGAR scores at 1 min and 5 min
Neonatal seizures
Neonatal respiratory morbidity
Uncontrolled hypertension
Pregnancy prolongation
Rate of preeclampsia
Rate of induction of labour
Mode of delivery
Postnatal readmission rate
Second trimester mean systolic and diastolic BP
Third trimester mean systolic and diastolic BP
Postnatal mean systolic and diastolic BP
Mean systolic and diastolic BP obtained in clinic setting
Area under the BP curve
Proportion of readings within target (< 140/90 mmHg)
Episodes of severe hypertension > 160/100 mmHg
Time to medication institution (weeks’ gestation)
Number of medication dose escalations

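### Patient satisfaction is a secondary outcome to be surveyed in every participant, but no instrument common to both arms measures it, so the plan yields no between-arm comparison of satisfaction

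*Protocol article*

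**What the plan says.** Satisfaction appears in the protocol article at four levels.

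- **Motivation.** The Abstract's Background says of remote monitoring: "This has the potential to be cost-effective, increase patient satisfaction, and reduce outpatient visits".
- **Aim.** The Abstract's Methods paragraph includes "impact on healthcare utilisation and end-user satisfaction of remote blood pressure monitoring" among what will be evaluated. The main Methods section says: "We will evaluate foetal outcomes as the primary outcome, in addition to maternal outcomes, patient satisfaction and the cost-effectiveness of this strategy".
- **Outcome.** Outcome measures states: "Other secondary outcomes will consist of maternal outcomes, feasibility and patient satisfaction, quality of life, healthcare utilisation and cost-effectiveness". Satisfaction and quality of life are separate entries in that list.
- **Measurement.** The text below the last block of Table 3 (Quality of life and patient satisfaction) says: "The satisfaction and quality of life of every participant will be surveyed with the EuroQol-5D-3L [41], State Trait Anxiety Inventory", and completes the list with the Edinburgh Postnatal Depression Score. These go out by email at baseline, at 28 weeks' gestation and 6 weeks after delivery.

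In addition, "participants in the interventional arm will complete investigator-designed surveys to assess the technological feasibility of remote monitoring". Table 3 marks these surveys and the qualitative interviews as interventional arm only. The text describes the interviewees as clinicians and midwives in the study and a group of consenting women from the remote arm.

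The section on data handling and analysis plans a comparison of the questionnaires at each time point.

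**The concern.** The article names an outcome, says it will be measured in every participant, and assigns it to instruments that measure other things. This is not detail left to a fuller protocol or to a statistical analysis plan. The instruments are listed, allocated by arm and tied to a construct, and the tie is wrong. An analysis plan cannot repair it later, because satisfaction data not collected from control women cannot be analysed.

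What is at stake is one secondary outcome. Under the plan as written, the trial can compare quality of life, anxiety and depression between arms, and it can describe remote-arm feedback. It cannot say whether women were more, less or equally satisfied with remote monitoring than with clinic visits.

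**Working it through.** No arithmetic beyond counting applies. The check sets each source under Table 3's quality-of-life and satisfaction heading against the arm that receives it and the construct the article attaches to it.

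| Source | Arm | Construct, from the article |
|---|---|---|
| EuroQol-5D-3L | Both | Quality of life (the cost-utility paragraph describes it as an index of quality of life, used to derive QALYs) |
| State Trait Anxiety Inventory | Both | Anxiety, by name |
| Edinburgh Postnatal Depression Score | Both | Depression, by name |
| Investigator-designed surveys | Remote only | Technological feasibility |
| Qualitative interviews | Remote-arm women, plus clinicians and midwives | Experience of the study |

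1. **Sources in both arms:** 3 of 5.
2. **Of those 3, sources whose name or description is satisfaction:** 0.
3. **Sources through which a control woman could rate her monitoring:** 0. The Sample size section plans 130 women per arm, so 0 of 130 control women would supply a satisfaction rating on a named instrument.
4. **Could the shared questionnaires be meant to stand for satisfaction?** The list of secondary outcomes separates satisfaction from quality of life, so the EuroQol result already has its own place. The three questionnaires are also sent at baseline, when a woman has no experience of the allocated monitoring to rate.
5. **Could another listed outcome fill the gap?** Table 3 includes compliance with face-to-face consultations, with no restriction to the remote arm. That is a behavioural indicator of acceptability, not a rating. Visits are counted in both arms, and patient time and travel are costed. These measure burden and resource use, not satisfaction.
6. **Does the planned analysis supply a comparison?** It compares questionnaires at each time point. Between arms it can use only the three shared instruments, so it yields comparisons of quality of life, anxiety and depression.

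Even within the remote arm, no survey is expressly a satisfaction measure, because the stated purpose of the investigator-designed surveys is technological feasibility.

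**The case against.** The strongest reply is that the trial never promised a randomised comparison of satisfaction. The aims in the Abstract and in Methods can be read as satisfaction with remote monitoring, which control women cannot rate and for which remote-arm surveys and interviews are suitable. The reference to increased satisfaction is background motivation. No hypothesis or contrast on satisfaction is stated, and the sentence about every participant may be loose drafting under a joint heading. This reading of the aims is fair and stands. It does not dispose of the point, because the measurement sentence still says that satisfaction will be surveyed in every participant, and satisfaction is a separate secondary outcome. If the one-arm reading is intended, that sentence needs correcting.

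Three stronger inferences are tempting, and the document does not support them.

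- **That the case for adoption rests on satisfaction.** The Abstract's discussion and the main Discussion rest it on clinic visits, waiting times, travel costs, compliance and rural access, and the economic section adds reduced costs.
- **That anxiety or quality-of-life scores will be reported as satisfaction.** Nothing commits the investigators to that. Where the article explains its use of the EuroQol instrument, it calls it quality of life.
- **That particular topics are absent from the questionnaires item by item.** Neither the contents of the three shared instruments nor those of the investigator-designed surveys are shown. Only the constructs can be judged, from names and stated purposes.

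It can also be said that ratings in an unblinded trial are open to expectation effects, and that recruitment began in July 2022 with a planned end in September 2023. Both are true. They limit what an added scale can deliver, but give no reason to leave the wording as it is.

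**Conclusion.** The point holds as a mismatch between a stated secondary outcome and the instruments assigned to it. Satisfaction is listed separately from quality of life and is said to be surveyed in every participant. Yet no satisfaction instrument is common to both arms, and the control arm has none at all. As written, the plan gives no between-arm comparison of satisfaction.

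The conclusion rests on two assumptions: that the three shared questionnaires measure what their names and the article's own description say, and that Table 3 is a complete list of the participant-reported sources. If the full protocol gives both arms a further satisfaction measure, the article's list is incomplete and should name it.

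The effect is confined to this outcome. The primary composite, the non-inferiority margin, and the cost and utilisation comparisons are untouched. The three shared questionnaires remain worthwhile for what they do measure; the Background itself notes that frequent monitoring can cause anxiety. The point should be put right, but it does not threaten the trial's main conclusion.

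**What to change.** **Preferred.** Add a few satisfaction-with-monitoring items, worded to fit both clinic and remote care, to the existing 6-week postpartum email survey in both arms. Compare them between arms as a secondary outcome. Describe the EuroQol-5D-3L, the State Trait Anxiety Inventory and the Edinburgh Postnatal Depression Score as quality of life, anxiety and depression only. Report that the ratings are unblinded, and give the number of women in each arm who had passed the survey before the items were added and so lack the measure.

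**If that is no longer practical.** Make the same relabelling of the three shared questionnaires. State that satisfaction or acceptability is assessed descriptively in the remote arm, with no randomised comparison.

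**Cost.** The preferred change adds a minute or two per woman to a survey already being sent, plus a short amendment submitted to the ethics committee. Given the recruitment dates, it may miss some women. The fallback changes wording only and needs no new data.

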### Sample size

The sample size calculation is based on the assumption that the composite foetal outcome will be equal in the remote BP monitoring and control groups: a non-inferiority trial. Prior data indicates that the rate of the composite foetal outcome is approximately 31.1%, drawn from a study previously undertaken in the local high-risk pregnant population [4]. Investigators made a reasoned choice about the acceptable difference in adverse foetal outcome and feasibility of the trial. As a result, the non-inferiority margin was defined as a 15% absolute increase or less in the remote BP monitoring group. With a one-sided α of 0.05, the study will achieve a power of 0.80 if 118 women will be included in each trial arm. Furthermore allowing for a 20% attrition rate, 260 participants will be needed in total, 130 participants in each arm.

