### Design and setting

The REMOTE Control trial will recruit patients across 3 metropolitan Australian teaching hospitals; Liverpool, Campbelltown and Bankstown Hospitals. Within these hospitals, women at high risk of developing a hypertensive disorder of pregnancy are referred to specialist obstetric medicine clinics, where their blood pressure is monitored regularly throughout their pregnancy, leading to an additional 6–8 clinic reviews. The non-inferiority trial will compare remote blood pressure monitoring with conventional clinic monitoring in a 1:1 allocation ratio.

The trial has been prospectively registered with the Australian and New Zealand Clinical Trials Registry (ACTRN12620001049965p) in October 2020. Ethics approval was granted by the South Western Sydney Local Health District human research ethics committee (SWSLHD HREC) in June 2021.

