The dichotomous primary outcome will be analysed using a generalised linear model (with binomial distribution and log link), adjusting for minimisation variables, chronic hypertension and aspirin use. Treatment effects will be expressed as adjusted risk ratios with 95% CIs. The secondary outcomes that are binary will be analysed using the same methods described for the primary outcomes, with corresponding 95% CIs. For those secondary outcomes that are continuous, data that is normally distributed will be analysed with parametric tests and non-normally distributed data will be analysed with non-parametric tests. Significance will be set at 0.05 and adjustments for multiple comparisons will be made where comparing several groups.

Subgroup analyses will be undertaken on (i) variables used in the minimisation algorithm (i.e. hypertension type [chronic or gestational hypertension] and LDA use); and (ii) other variables of prognostic significance pre-specified as ethnicity, body mass index, prior severe hypertension in the index pregnancy, antihypertensive therapy at randomisation, gestational diabetes mellitus at randomisation, and smoking status at randomisation. Subgroup analyses will be limited to the primary outcome. Results will be presented as adjusted risk ratios with 95% confidence intervals. The results of subgroup analyses will be treated with caution and will be used for the purposes of hypothesis generation only.

Participants with missing primary outcome data will not be included in the primary analysis in the first instance. This presents a risk of bias, and sensitivity analyses will be undertaken to assess the possible impact of the risk. Sensitivity analyses will also be undertaken for the women who were randomised to the conventional care arm, who had a remote blood pressure monitor at home. A post-hoc analysis will be undertaken for aspirin compliance as a modifier based on PFA-100 levels.

Comparison of questionnaires will be made for each time point.

A’within trial’ economic evaluation will be conducted alongside the trial from a health sector perspective, and extending to patient and carer costs. This will combine three forms of complimentary economic analysis in a comprehensive approach.

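### The sample size uses a one-sided alpha of 0.05, but the only interval planned for the primary outcome is a 95% CI, and the deciding limit is not stated

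*Protocol article*

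**What the plan says.** The protocol article describes a two-arm non-inferiority trial: "The non-inferiority trial will compare remote blood pressure monitoring with conventional clinic monitoring in a 1:1 allocation ratio" (Design and setting).

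Its Sample size section fixes the design values:

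- **True effect:** "The sample size calculation is based on the assumption that the composite foetal outcome will be equal in the remote BP monitoring and control groups".
- **Event rate, in per cent:** "Prior data indicates that the rate of the composite foetal outcome is approximately 31.1".
- **Margin:** "the non-inferiority margin was defined as a 15% absolute increase or less in the remote BP monitoring group".
- **Error rate, power and size:** "With a one-sided α of 0.05, the study will achieve a power of 0.80 if 118 women will be included in each trial arm".

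The section Data handling, analysis and result reporting specifies a log-link binomial model for the primary outcome and gives the form of the result: "Treatment effects will be expressed as adjusted risk ratios with 95% CIs". Later in the same paragraph, after the methods for the secondary outcomes, it adds "Significance will be set at 0.05" without saying whether this is one-sided or two-sided.

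The article mentions neither a 90% interval nor a one-sided 95% bound. No sentence says which confidence limit is to be compared with the margin.

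**The concern.** A non-inferiority test at one-sided 0.05 is the same as asking whether the upper limit of a two-sided 90% interval lies below the margin. Using the upper limit of a two-sided 95% interval halves the one-sided error rate to 0.025. The article therefore sizes the trial at one level and presents its primary result at another.

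This matters for the trial's main conclusion. Some results would meet the margin on the 90% limit and miss it on the 95% limit, and for those the safety claim depends on a rule that the article does not give. If the stricter limit applies, the stated power is too high. If the more lenient one applies, the planned primary output does not show the limit on which the conclusion rests.

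**Working it through.** **Inputs** (all from the Sample size section, except the 95% level from the analysis section): event rate p = 0.311 in both arms, true difference 0, margin 0.15 absolute, 118 per arm, one-sided alpha 0.05, power 0.80.

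**Step 1. Reproduce the plan's figure.** With the unpooled normal approximation,

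n per arm = 2p(1 − p)(z₁₋α + z₁₋β)² / margin²

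- 2 × 0.311 × 0.689 = 0.42856
- one-sided 0.05: 0.42856 × (1.645 + 0.842)² / 0.0225 = 117.8, so 118. This matches the article.
- one-sided 0.025: 0.42856 × (1.960 + 0.842)² / 0.0225 = 149.5, so 150.

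Of these two levels, only one-sided 0.05 gives 118. A Farrington-Manning calculation gives 117 at one-sided 0.05, so the choice of variance method does not explain the gap.

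**Step 2. Power at 118 per arm under each limit.**

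SE = √(0.42856 / 118) = 0.0603, and power = Φ(0.15 / SE − z₁₋α).

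| Deciding limit | One-sided alpha | Argument of Φ | Power |
|---|---|---|---|
| Upper limit of 90% CI | 0.05 | 2.489 − 1.645 = 0.844 | 80.1% |
| Upper limit of 95% CI | 0.025 | 2.489 − 1.960 = 0.529 | 70.2% |

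The Farrington-Manning version gives 80.3% and 70.5%. If all 130 randomised women per arm were evaluable, the 95% limit would still give only 74.3% (SE = √(0.42856 / 130) = 0.0574; 0.15 / 0.0574 − 1.960 ≈ 0.65).

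**Step 3. Results for which the choice matters.** Holding the SE at 0.0603, the largest observed increase that still meets the margin is:

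- 90% limit: 0.15 − 1.645 × 0.0603 = 0.051
- 95% limit: 0.15 − 1.960 × 0.0603 = 0.032

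An observed excess between about 3.2 and 5.1 percentage points passes on one limit and fails on the other. Under the plan's own assumptions this happens in 80.1% − 70.2% ≈ 10% of trials. That is the power difference expressed another way, not a further effect.

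**Step 4. The scale.** Steps 1 to 3 concern an unadjusted risk difference, the scale used for sizing. The planned interval is for an adjusted risk ratio, which cannot be compared directly with an absolute margin. As an illustration only, assume the margin is converted at the planning rate: (0.311 + 0.15) / 0.311 = 0.461 / 0.311 = 1.48. Then SE(log RR) = √(2 × 0.689 / (0.311 × 118)) = 0.194 and ln 1.48 = 0.394. Power is Φ(0.394 / 0.194 − 1.645) ≈ 65% on a 90% limit and Φ(0.394 / 0.194 − 1.960) ≈ 53% on a 95% limit. The article makes no such conversion. The figures show only that 70% is not the power of the planned risk-ratio interval.

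**The case against.** The strongest reply is that the analysis section says how effects will be presented, not how non-inferiority will be decided. The only error rate tied to the non-inferiority hypothesis is the one-sided 0.05 in the Sample size section, and at that level the stated 80% is right. This stands: the 70% is conditional on the 95% interval deciding.

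Second, the general significance level of 0.05 is weak evidence either way. It follows the secondary-outcome methods, in a sentence that goes on to multiple comparisons, and it is compatible with a one-sided 0.05 test. This also stands, and the point does not rest on it.

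Third, an analysis plan that is not shown may name the deciding limit. That is possible, so a reader should not conclude that the choice has been left open until results are known. It does not remove the point, because the article states two levels that do not match, and any later document has to reconcile them.

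Fourth, deciding on the 95% limit would be stricter and would not raise the risk of a false non-inferiority claim. That is correct; what would be lost is power.

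**Conclusion.** The point holds as a mismatch between two stated levels, with no stated rule to connect them. The sizing uses one-sided 0.05; the only interval planned for the primary outcome is at 95%, whose upper limit is a one-sided 0.025 test.

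The size of the problem depends on which limit decides:

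- **95% interval decides:** power is about 70% at 118 per arm, against the stated 80%, and 150 evaluable women per arm would be needed for 80%.
- **One-sided 0.05 decides:** power is 80% as stated, and the defect is that the planned output lacks the deciding limit.

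These figures assume a 31.1% rate in both arms, no true difference, a conventional two-sided 95% interval and an unadjusted risk difference.

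A reader might infer that the trial simply has 70% power. The article does not support that: it nowhere says that the 95% limit is the non-inferiority test, and the 70% does not describe the risk-ratio interval that is planned. Whether the allowance for attrition is adequate is a separate question and is not part of this shortfall.

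**What to change.** Before outcome data are analysed, state in the protocol and analysis plan that non-inferiority is decided by the upper limit of the two-sided 90% confidence interval (one-sided 0.05) for the absolute risk difference, compared with the 15-point margin. Say explicitly that the risk difference is added as the effect measure for this decision, because the planned risk ratio cannot be set directly against an absolute margin. Report the 95% interval alongside; the adjusted risk ratio can remain as a reported measure. This keeps the sample size, alpha and stated power. It costs wording and one additional effect estimate.

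Alternatively, keep the 95% interval as the deciding one, again on the risk-difference scale. Then restate alpha as one-sided 0.025 and power as about 0.70 at 118 per arm. This also costs only wording, but the stated power is less favourable.

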**Exclusion criteria**	
Participants who have signs of preeclampsia on initial evaluation	Preeclampsia (BP reading > 140 mmHg and/or 90 mmHg on at least 2 occasions after 20 weeks’ gestation accompanied by evidence of end-organ involvement)
Multifoetal pregnancy	
Lethal foetal abnormality	Lethal foetal chromosomal, genetic or morphological abnormality detected on screening tests
Inability to access or use the app-based system	
Unable to consent	
Non-English speaking background not supported by the mobile application	

*GFR* glomerular filtration rate, *SLE* systemic lupus erythematosus, *BP* blood pressure, *HDP* hypertensive disorder of pregnancy

Participants will be recruited through both the antenatal and specialist obstetric medicine clinics. Eligible patients will undertake full informed written consent with an Obstetric Physician or research midwife. Consented participants will be randomised in a 1:1 ratio, to receive either conventional care with face-to-face consultations or remote BP monitoring. Computer-generated randomisation will occur through RedCAP™, and a minimisation protocol for the variables chronic hypertension, centre of treatment and aspirin use will be instituted. Individual patient randomisation will be used so that treatment allocation remains unpredictable. To avoid bias, the random allocation sequence is concealed from those responsible for recruiting women into the study, and generated by the REDCap randomisation module. A research midwife based at each site will be responsible for consenting and assigning participants to the trial arms. Blinding of the treatment allocation to the patient and treating physician will be difficult and unethical. Outcome assessors and data analysts will not be blinded to treatment allocation. An overview of the study procedures is shown in Fig. 1.

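### The 20% attrition allowance is miscalculated: 260 women cover about 9% loss, and at 20% loss power is about 76%, not 80%

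*Protocol article*

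**What the plan says.** The Sample size section gives every input to the calculation. The trial is planned on the assumption that "the composite foetal outcome will be equal in the remote BP monitoring and control groups: a non-inferiority trial". From earlier local data, "the rate of the composite foetal outcome is approximately 31.1" per cent, and "the non-inferiority margin was defined as a 15% absolute increase or less in the remote BP monitoring group". The power statement follows: "With a one-sided α of 0.05, the study will achieve a power of 0.80 if 118 women will be included in each trial arm". The next sentence turns this into the recruitment target: "Furthermore allowing for a 20% attrition rate, 260 participants will be needed in total, 130 participants in each arm".

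Two other places bear on the point. Under Study population, "Consented participants will be randomised in a 1:1 ratio", so the arms are equal in size. Under Data handling, analysis and result reporting, "Participants with missing primary outcome data will not be included in the primary analysis in the first instance".

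**The concern.** The power statement needs 118 women per arm in the analysis. The recruitment target is 130 per arm and is said to allow for 20% attrition. Twenty per cent of 130 is 26, which leaves 104, or 14 fewer per arm than the preceding sentence requires. Both sentences cannot be right.

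What is at stake is the planned power for the primary outcome. In a non-inferiority trial, lost power means a greater chance of an inconclusive result when remote monitoring is in truth no worse than clinic monitoring. The Abstract and the Discussion present the trial as powered for maternal and foetal outcomes, so readers will rely on this figure.

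**Working it through.** **Inputs** (Sample size section, unless noted): event rate p = 0.311 in both arms; true difference 0; margin 0.15 on the absolute scale; one-sided α = 0.05 (z = 1.645); power 0.80 (z = 0.842); attrition 20%; 130 per arm randomised. Allocation is 1:1 (Study population).

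**Step 1. Reproduce the evaluable number.**

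n per arm = (1.645 + 0.842)² × 2 × p(1 − p) / 0.15²
= (1.645 + 0.842)² × 2 × 0.311 × 0.689 / 0.0225
= 117.8, rounded up to **118**.

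This matches the plan exactly, so the starting figure is sound and the fault lies in the attrition step.

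**Step 2. Apply 20% attrition to 118 per arm.**

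- Division by the retained fraction: 118 / 0.80 = 147.5, so **148 per arm, 296 in total** (236 / 0.80 = 295 before rounding to equal arms).
- The weaker method of adding 20%: 118 × 1.20 = 141.6, so 142 per arm, 284 in total.
- Stated: 130 per arm, 260 in total.

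The stated figure matches neither method. Against the first, it is short by 148 − 130 = 18 per arm, 36 in total.

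**Step 3. What 130 per arm does cover.**

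- Maximum loss that still leaves 118: 1 − 118/130 = **9.2%**.
- Inflation actually applied: 130/118 − 1 = 10.2%.

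Two routes do arrive at the stated figure. One inflates by 10% (118 × 1.10 = 129.8). The other adds 20% of a single arm to the two-arm total (0.20 × 118 = 23.6, rounded to 24; 236 + 24 = 260). Neither is a 20% allowance. The article does not say which route, if either, was used.

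**Step 4. Power at the numbers in question.**

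Power = Φ(0.15 / √(2 × 0.311 × 0.689 / n) − 1.645)

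| Analysed per arm | Situation | Power | Farrington–Manning check |
|---|---|---|---|
| 130 | no loss | 83.3% | 83.5% |
| 118 | 9.2% loss | 80.1% | 80.3% |
| 104 | 20% loss (260 × 0.80 = 208 in total) | **75.5%** | 75.8% |

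At 20% loss the chance of missing non-inferiority with truly equal arms is 100 − 75.5 = 24.5%, against 100 − 80.1 = 19.9% with 118 per arm.

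**The case against.** The arithmetic contradiction itself is hard to dispute: no usual attrition convention leads from 118 to 130 at 20%. The reasonable objections concern its consequence.

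- **Attrition need not mean a missing primary outcome.** The Sample size section does not define attrition. The foetal outcomes come from the electronic medical record at delivery, and the analysis is primarily by intention to treat. A woman who stops monitoring or ignores the surveys may still have a recorded outcome. This stands in part: the 75.5% applies only if the full 20% lack the primary outcome. It is still the ordinary meaning of an attrition allowance in a sample size calculation, particularly as the first analysis leaves out women without that outcome. If losses are expected to be small, that argues for stating about 9%. It does not make 20% correct.
- **Imputation is planned.** The plan includes analyses with and without imputed data. These do not replace the complete-case primary analysis, and imputation does not in general restore the information in outcomes that were never observed.
- **The loss of power is modest.** This is true: about 4.5 points at the full 20% loss, none below the planned 80% until loss exceeds 9.2%, and a small gain if nobody is lost.
- **The decision interval is a separate matter.** The article plans 95% confidence intervals. If a two-sided 95% interval on the absolute difference decided non-inferiority (one-sided 0.025), power would be 64.7% with 104 per arm, but it would already be 70.2% with 118. Most of that fall comes from the interval and not from attrition. The planned interval is moreover for an adjusted risk ratio, and the article does not say that it decides non-inferiority. The 64.7% is therefore not counted as a consequence of this error.

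**Conclusion.** The concern holds. The statement that 260 women allow for 20% attrition is wrong as written, and nothing elsewhere in the article corrects it. On the plan's own inputs, 260 women allow for 9.2% loss at 80% power. At 20% loss they give about 76% power, a shortfall of about 4.5 points.

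The attrition shortfall rests only on the article's own figures. The power figure assumes in addition that the 20% lost have no primary outcome, that loss is equal in the two arms, and that non-inferiority is tested on the absolute difference at one-sided 0.05, as in the sample size calculation. The effect on the trial is moderate, but a headline design figure for the primary outcome should be correct, and it would otherwise be carried into the report of the results.

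**What to change.** Correct the one sentence in the Sample size section so that the number recruited, the attrition and the power agree. Any one of these does so:

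1. Keep 260 and 80% power: state that 130 per arm allow for about 9% loss of primary outcome data while leaving 118 per arm.
2. Keep 260 and 20% attrition: state that 104 per arm would remain, with about 76% power.
3. Keep 20% attrition and 80% power: raise the target to 296 (148 per arm).

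The sentence should also say that attrition here means a missing primary outcome, since that is what reduces the analysed number. Options 1 and 2 cost one sentence and a slightly less favourable figure, with no extra recruitment. Option 3 costs 36 more women.
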